## Abstract

**Methods::**

Sixty advanced esophageal cancer patients post-feeding jejunostomy will be divided into 2 equal groups, an intervention group (n = 30) and a control group (n = 30). Patients in the intervention group will receive acupuncture using the following acupoints: ST36 (Zusanli), ST37 (Shangjuxu), ST39 (Xiajuxu), PC6 (Neiguan), LI4 (Hegu), and Liv 3 (Taichung). Patients in the control group will receive shallow acupuncture on 12 non-acupoints (sham points), 1 cm from the above mention points. Patients and assessors will be blind to trial allocation. Both groups will receive acupuncture twice a week for 6 weeks. The main outcome measurements are: body weight, BMI, Sigstad’s score, and the Arts’ dumping questionnaire.

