
Acupuncture is a treatment that was previously shown to reduce diarrhea for irritable bowel syndrome patients^[17,18]^ along with a reduction in gastroparesis syndrome.^[19,20]^ Acupuncture was also shown the ability to regulate gastrointestinal mobility through different physiological pathways.^[21]^ Acupuncture decreased the fasting glucagon-like peptide-1 levels in an animal model^[22]^ and also showed the ability to decrease insulin and glucagon levels.^[23]^ In oncological patients, acupuncture reduced chemotherapy-related abdominal pain, nausea, vomiting, and diarrhea with good safety.^[24–26]^ We have chosen to compare acupuncture to shallow needling on sham non-acupoint in order to generate a reliable placebo effect that resembles acupuncture intervention processes.

There are no previous studies that have examined the direct use of acupuncture on dumping syndrome. The goal of this single-blind randomized control trial is to investigate the effect of acupuncture on dumping syndrome in esophagus cancer patients with jejunostomy tube feeding. We hypothesize that acupuncture will be superior to sham acupuncture in regulating dumping syndrome.

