## 2. Methods

### 2.1. Study design and settings

This single-blind randomized control trial will be implemented in the Department of thoracic surgery of China medical university hospital (CMUH), Taichung City, Taiwan. The study will be initiated on February 2023 and will be concluded until January 2025. This single center study will use a 1:1 ratio parallel group allocation. Informed consent will be obtained prior to the patient’s enrollment. The 2 groups are an intervention group (INT) and a control group (CON). The study was approved by the institutional review board (IRB) of CMUH (approval no. CMUH111-REC3-004) and a study protocol registration online on https://clinicaltrials.gov/ct2/show/NCT05801666 (registration no. NCT05801666). The study aims to examine the effect of acupuncture on preventing and treating dumping syndrome in esophagus cancer patients after feeding jejunostomy surgery. The study will also measure the effect of acupuncture on preventing malnutrition using body weight and body mass index (BMI) (see Fig. 1). In this study, both the patients and the assessors of outcome measurements will be blinded to the group’s allocation.

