### 2.12. Outcome measures

Main outcome measurements are: body weight, BMI (will be measured weekly) dumping syndrome questioners: the Sigstad’s score in order to determine the diagnosis of dumping syndrome and the Arts’ dumping questionnaire in order to assess early or late dumping syndrome (will be measured on the baseline, week 3, week 6) (see Figure S1, Supplemental Digital Content, http://links.lww.com/MD/J34 for the Sigstad’s score and Figure S2, Supplemental Digital Content, http://links.lww.com/MD/J35 for the Arts’ dumping questionnaire).

The secondary outcomes are: muscle grip strength test (measured weekly in kg) (by electronic hand grip test model EH101 manufactured by “CAMRY,” China), blood test: Complete Blood Count, kidney and electrolytes (measured as adjuvant adjuvant concurrent chemoradiation therapy schedule), pre-albumin, albumin level, glucose blood levels, inflammation data including Erythrocyte Sedimentation Rate and C-reactive protein (measured at baseline and on week 6). Total Intensive care unit stay, total hospital stay, and total mechanical ventilation in days will be measured 6 months after inclusion. Mortality will be measured at 3 months, 6 months. Medical charts and drug use will also be measured (Fig. 4). All measurements will be measured by nurses and doctors in the department that are blind to the study group allocation.

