Limitations of the study include a specific Taiwanese population and cannot be generalized to other populations. This study is also only a single-center study. The study protocol could not apply a double-blind design due to the type of intervention (manual acupuncture). The study will investigate the role of acupuncture in the prevention of dumping syndrome and malnourishment, the study does not require a positive Sigstad’s score to verify dumping syndrome as a condition for inclusion, therefore it is possible that the number of patients that will develop dumping syndrome could be low, in this case, the study will focus on body weight and BMI as the main outcomes to assess the prevention of malnourishment. The study did not specify the cancer stage in the inclusion criteria. High mortality rates in Esophagus cancer might impair the completeness of the data and can increase the levels of missing data.

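### The limitations text narrows the main outcomes to weight and BMI if few patients develop dumping, an undefined post-randomisation trigger that a true preventive effect would itself make more likely

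*Protocol article*

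**What the plan says.** The Introduction states the hypothesis: "We hypothesize that acupuncture will be superior to sham acupuncture in regulating dumping syndrome". Section 2.1 gives the aim in the same terms: "The study aims to examine the effect of acupuncture on preventing and treating dumping syndrome in esophagus cancer patients after feeding jejunostomy surgery". It then adds prevention of malnutrition, measured by weight and BMI, as something the study will also examine.

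The Abstract lists the outcomes without ranking them: "The main outcome measurements are: body weight, BMI, Sigstad’s score, and the Arts’ dumping questionnaire". Section 2.12 repeats the list. Weight and BMI are taken weekly, while the two dumping instruments "will be measured on the baseline, week 3, week 6". Section 2.16 applies a single 0.05 significance level to everything and gives no order or adjustment among the main outcomes.

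The last paragraph of section 3 (limitations) then makes the list conditional. It notes that "the study does not require a positive Sigstad’s score to verify dumping syndrome as a condition for inclusion" and continues "therefore it is possible that the number of patients that will develop dumping syndrome could be low". The consequence it draws is that "in this case, the study will focus on body weight and BMI as the main outcomes to assess the prevention of malnourishment". Nothing elsewhere in the article qualifies or overrides this.

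**The concern.** The worry behind the sentence is legitimate: with no dumping requirement at entry, there may be little dumping to compare. The remedy is the problem, for two reasons.

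- **The trigger is an effect of treatment.** The number who develop dumping becomes known only during follow-up, and half the patients receive a treatment intended to lower it. If acupuncture works as hypothesised, the count falls, and the rule then moves the trial away from the outcome on which it worked.
- **The trigger is open.** The text does not say how few is low, at which visit the count is taken, whether it is pooled or by arm, or whether the decision comes before the comparative results are known. The choice of main outcomes could therefore be made with those results in view.

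At stake is which question the trial is reported as having answered.

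**Working it through.** **1. The plan's own sample size (section 2.14).** Inputs: two-tailed t test, d = 0.8, 80% power, 15% drop-out, 60 patients. Alpha 0.05 is from section 2.16.
- The exact two-sample t calculation gives 25.52, so 26 per group, or 52 in total.
- 52 × 1.15 = 59.8, so 60, which matches the stated total. Dividing instead, 26/0.85 = 30.6, so 31 per group and 62 in total.
- The article calls 26 a total. It reproduces only as a per-group number; 13 per group would give about 50% power.
- Power for one test at 0.05 is 80.7% with 26 completers per group and 86.1% with 30.

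**2. Can a true effect trigger the switch?** Let p be the control-arm rate of dumping, RR the risk ratio and c the cut-off for low. With 30 patients per arm:

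P(switch) = P(X₁ + X₂ ≤ c), where X₁ ~ Binomial(30, p) and X₂ ~ Binomial(30, p × RR).

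The expected count is 30p(1 + RR). The range of p, 20–50%, is the prevalence cited in the Introduction, used here as an assumed on-trial rate. The values of c and RR are assumptions, because the article gives none.

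| p | c | RR | Expected cases of 60 | P(switch) |
|---|---|---|---|---|
| 0.20 | 9 | 1 | 12 | 21% |
| 0.20 | 9 | 0.5 | 9 | 59% |
| 0.20 | 9 | 0.25 | 7.5 | 79% |
| 0.35 | 15 | 1 | 21 | 7% |
| 0.35 | 15 | 0.5 | 15.75 | 48% |
| 0.35 | 15 | 0.25 | 13.1 | 79% |
| 0.50 | 15 | 1 | 30 | 0% |
| 0.50 | 15 | 0.5 | 22.5 | 2% |
| 0.50 | 15 | 0.25 | 18.75 | 16% |

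The direction is the same in every block: the stronger the prevention, the likelier the switch. The size is large at low and middle rates and small at 50%.

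**3. Type I error.**
- Success claimed on either of two independent families at 0.05: 1 − 0.95² = 9.75%.
- Success claimed on any of four independent tests: 1 − 0.95⁴ = 18.5%. This is a loose bound, since weight and BMI move together.
- Null simulation of a dumping measure and a weight measure (40,000 runs per correlation, 30 per arm, correlations 0 to −0.8): claiming on either gives 9.7% down to 8.2%.
- Same simulation, with a fixed cut-off on the pooled count choosing which of the two is tested: 4.8–5.2%.

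The first two figures arise whenever several unranked main outcomes share one 0.05 level, with or without the switch. A pre-set rule on the pooled count does not inflate the error.

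**4. What the alternatives cost in power (d = 0.8, 26 completers per group).**
- One primary at 0.05: 80.7%.
- Two families at 0.025 each: 71.6%; 80% power would need 31 per group, or 37 per group (74 in total) after 15% drop-out.
- Four outcomes at 0.0125 each: 61.7%; 80% power would need 37 per group, or 44 per group (88 in total) after drop-out.

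**The case against.** The best defence is that weight and BMI are already main outcomes, listed first in the Abstract and in section 2.12, and that preventing malnutrition is a declared aim in section 2.1. That stands. A reader might infer that a secondary outcome is promoted over the primary; in fact the rule narrows four main outcomes to two.

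A reader might also infer that the choice will be made after the arms have been compared. The text speaks only of a number of patients, and patients and assessors are blinded. The wording permits an unblinded choice but does not state one.

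A third tempting reading is that the switch raises the false-positive rate from 5% to 9.75%. It does not: the plan without the switch does not hold 5% either, because four main outcomes share one level.

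The trigger probabilities rest on assumed cut-offs and risk ratios, and at a 50% control rate with risk ratio 0.5 the chance is only 2%. The 20–50% is a cited prevalence among esophageal cancer patients, not an incidence on trial, and the baseline-status subgroup in section 2.16 implies that some patients may already have dumping at entry. These limits stand too.

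Finally, the sentence sits among limitations, section 2.16 covers all measurements, and a separate analysis plan might define low. So the dumping results need not go unreported, and it would go too far to call the trial uninterpretable. But the sentence is worded as a plan. A cut-off on the same count would settle the alpha question and still let a true effect move the trial off its own hypothesis.

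**Conclusion.** The point holds as a badly fixed rule, not as missing detail. The main outcomes are made to depend on a post-randomisation count that the treatment is designed to lower, with no definition of low and no safeguard on when the choice is made.

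How often a true effect would trigger the switch cannot be determined from the document. Under the assumptions shown, halving the dumping risk raises the chance from 21% to 59% at a 20% control rate (9 or fewer cases) but only from 0% to 2% at 50% (15 or fewer).

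The 9.75% to 18.5% type I error is an upper bound belonging to the unranked main outcomes, so deleting the switch alone would not restore 5%. The rule decides which question the trial answers and costs only wording to replace, so it should be corrected.

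**What to change.** - Delete the conditional sentence in the limitations paragraph.
- Name one primary outcome and time point for the 0.05 test. Sigstad's score at week 6 matches the stated hypothesis. Change in body weight at week 6 is the alternative if the sponsor decides that malnutrition is the main question.
- Rank the remaining main outcomes as key secondary. Both steps are needed: removing the switch settles the trigger, and ranking settles the multiplicity.
- If a fallback is kept, base it only on a stated number of Sigstad-positive patients at baseline, pooled over arms. Baseline status is unaffected by treatment, but it does not measure new cases, so it only partly meets the concern about too little dumping.
- Make the change, in the protocol and the registration, before anyone examines post-baseline outcome data by arm. Before database lock is too late, because weekly weights and the week 3 and week 6 scores would already exist.

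Cost: wording only, and the other outcomes lose main status. The sample size need not change: power for the single primary stays at about 81% with 26 completers per group at d = 0.8.
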